### Study participants

#### Inclusion criteria

Adults over 18 years of age and under 80 years
Referred to the hepatobiliary surgical service at St James’s HospitalDiagnosed with any hepatic tumourOne of:Referred for liver resection of two or more Couinaud segments by multi-disciplinary team discussion at Saint James’s Hospital (Primary resection arm)Referred for PVE or ALPPS prior to likely major hepatectomy by multi-disciplinary team discussion at Saint James’s Hospital (PVE/ALPPS arm)

#### Exclusion criteria

Unable to consent independentlyPrevious liver resectionPrivate patientsConcurrent malignancy unrelated to liver tumourChronic renal failure (eGFR < 30 mL/min)Possible pregnancyOther contraindications to DGE-MRI, including:Cochlear ImplantAneurysm ClipsNeurological stimulatorImplanted cardiac devices (ICD, PPM, loop recorders, or any others)Metal heart valveHistory of metal foreign bodies in orbitsOther implanted metal device which prevents MR imagingKnown allergy to Gadolinium contrastClaustrophobiaWeight exceeding 250 kgMaximal diameter exceeding 55 cmOther contraindications to ICG, including:Known allergy to Indocyanine greenKnown allergy to sodium iodineKnown reaction or allergy to iodinePrevious diagnosis of a thyroid problemBreastfeeding

(*Hepatectomy Risk Assessment With Functional Magnetic Resonance Imaging - Full Text View -*
*ClinicalTrials.gov*, n.d.)*Hepatectomy Risk Assessment With Functional Magnetic Resonance Imaging - Full Text View -*
*ClinicalTrials.gov*. (n.d.). Retrieved September 30, 2021, from https://clinicaltrials.gov/ct2/show/NCT04705194

### Study procedures (resection arm)

HEPARIM will involve only a minimal deviation from the routine patient pathway (Fig. 1). In about 3/4 of participants the only investigations added for research purposes are the ICG measurements. The rest will not require a new MRI for surgery planning, and an additional pre-surgery MRI would therefore be performed for research purposes only. In the small number of PVE/ALPPS patients, the additional MRI is performed only for research purposes – see section on study procedures for the PVE/ALPSS arm.

**Fig. 1 Fig1:**
[figure not shown]
Pathway demonstrating patients route through the trial in both the primary surgical and portal vein embolisation arms. Items in blue are unique to trial patients

#### Recruitment

Patients considered for major liver resection will be identified at the Hepatobiliary multi-disciplinary team (MDT) meeting at St James University Hospital Leeds and contacted by phone. If they agree to finding out more about the study then an information pack will be posted to them, including a letter of invitation, the patient information sheet and an example consent form. Patients will have at least 3 days to consider this information, and after that they will be contacted by the member of their clinical care team to schedule the baseline visit.

#### Baseline visit

*Consenting*: Formal written consent will be obtained on the day of the visit. After consenting the participant will be assigned an anonymous study ID. If they don’t consent to participation, then only the MRI scans requested by the MDT will be collected and stored in their medical records, but no research data will be collected.

##### Questionnaires

An initial dataset will be captured incorporating the participant’s medical history and up-to-date investigations. This will be obtained through a combination of interview, review of paper notes and review of the electronic medical record. An MRI safety screening form will be administered. If a contraindication to MRI is found at this point, the visit will be cancelled, and the participant will be excluded from the study. An ICG safety questionnaire will be used to exclude participants with contraindications to ICG use. Participants excluded from ICG testing at this point will not be excluded from the study as other measures of liver function will still be available for analysis of secondary outcomes.

##### ICG measurement

Participants will be cannulated and ICG will be administered intravenously as a bolus dose of 0.5 mg/kg through the cannula. The ICG will be reconstituted with 5 ml of water for injection for every 25 mg of ICG, leading to a dilution of 5 mg ICG per 1 ml. Serial percutaneous ICG measurements will then be taken using an ICG clearance meter using a finger clip device (LiMON; Maquet, Germany). Participants will lie in the supine position and calibration will be performed before testing starts. In order to derive absolute ICG concentrations, we will also take two separate blood samples of 2.5 mL each, both after ICG injection (pre-operative). The samples will be processed and stored in a dedicated facility in the Leeds Institute for Cardiovascular and Metabolic Medicine (LICAMM) and analysed as a batch at the end of the study.

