MRI-based liver function tests based on uptake of the liver-specific contrast agent Gadoxetate offer a promising approach for assessment of FLR function in clinical practice [16]. Apart from wide availability, a major advantage of Gadoxetate as compared to ICG and tracers used in hepatobiliary scintigraphy is the low extraction fraction even in healthy liver. With a fast dynamic acquisition and a pharmacokinetic analysis of the data (dynamic Gadoxetate-enhanced MRI or DGE-MRI), this enables a separate quantification of liver perfusion and hepatocellular function, as well as structural parameters such as the extracellular volume fraction [17]. Previous studies on Gadoxetate MRI for liver surgery planning use descriptive or approximate measures of Gadoxetate uptake and therefore do not fully exploit the potential offered by this extra quantitative information [18–20]. Moreover, previous work tends to focus on HCC, but inhomogeneous liver function can be relevant even in patients with liver metastases due to the effects of chemotherapy-induced liver injury and obesity-associated liver disease [21].

A pilot study with DGE-MRI in 29 patients with colorectal liver metastases (CRLM), using post-operative bilirubin as a surrogate for liver function, suggested that DGE-MRI biomarkers significantly improved the predictions of post-operative function compared to biochemical markers and volumetric assessment of the FLR [22]. A parameter of particular interest was the normalised Gadoxetate clearance (GC), a combination of perfusion and function that determines the rate at which the liver clears Gadoxetate from the blood pool. GC has units of mL/min/kg and measures the volume of plasma (mL) fully cleared of Gadoxetate per minute and per kg body weight. Potentially, the GC of the FLR (FLR-GC) can offer a clear and widely available cut-off value to determine if a surgery is safe to perform, irrespective of the underlying disease or the body size of the patient considered for surgery.

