The primary aim of HEPARIM is to determine if DGE-MRI biomarkers of liver function and perfusion offer a significant improvement in the prediction of post-hepatectomy liver function. ICG clearance will be used as a reference measurement of post-operative liver function and correlated against DGE-MRI before surgery. As a secondary aim, DGE-MRI will be validated directly by performing ICG pre-operatively at the same time as the MRI and correlating the ICG clearance with whole-liver GC (WL-GC). A positive result on the primary aim can potentially improve the safety profile of hepatic surgery and open the door to extend the indication to wider groups of patients and avoid harmful interventions where they are not required.

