## Methods/design

### Objectives and outcome measures

#### Primary objective

To determine if DGE-MRI can improve predictions of post-hepatectomy liver function. The primary outcome measure is the correlation between preoperative FLR-GC (mL/min/kg) and ICG R15 1 day after surgery (%).

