#### Secondary objectives

To validate DGE-MRI based measurements of liver function against a gold-standard liver function test. The outcome measure is the correlation between preoperative WL-GC (mL/min/kg) and a simultaneously measured ICG R15 (%).To determine the relationship between volumetric and functional liver growth after PVE/ALPPS. Outcome measure is the correlation between growth in FLR volume and growth in FLR-GC after the first stage.To determine if preoperative DGE-MRI can improve predictions of PHLF (any grade) over and above routinely available data. HEPARIM will adopt the PHLF definition by the International Study Group of Liver Surgery (ISGLS).To determine if preoperative DGE-MRI can improve predictions of 90-day post-operative outcome over and above routinely available data. (*Hepatectomy Risk Assessment With Functional Magnetic Resonance Imaging - Full Text View -*
*ClinicalTrials.gov*, n.d.)

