#### In-patient follow-up

Once the participant’s surgery is complete, data obtained as part of the participant’s standard intra and post-operative care will be collected. This includes any blood tests during admission, the characteristics of the operation, complications and length of stay. Pathology results will be collected once reported. The ICG test with the finger-clip device will be repeated postoperatively at bedside to determine a reference value for postoperative liver function. This will be performed on day 1 post-surgery if feasible. A range of biochemical measures will be used to calculate postoperative liver function using the post-operative data set.

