#### Blood samples

Blood samples taken after ICG injection at the baseline visit will be processed in the LICAMM laboratories. Whole blood and blood plasma will be stored in a secure sample storage facility within LICAMM with access limited to LICAMM staff. Samples will be stored in a freezer and will only be accessed by members of the research team. ICG concentrations will be measured in batch after finalizing recruitment. The remaining samples will be stored for a maximum of 5 years to measure metabolomics data for secondary research. Precise use will be based on future research priorities. After 5 years any remaining samples will be destroyed according to standard LICAMM procedure for sample disposal.

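### Pre-operative absolute ICG concentrations serve no stated outcome, so whole-liver GC, a clearance, is validated only against R15, which also varies with ICG distribution volume

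*Protocol article*

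**What the plan says.** **The MRI measure is a clearance.** Background: "GC has units of mL/min/kg and measures the volume of plasma (mL) fully cleared of Gadoxetate per minute and per kg body weight".

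**The aims name a clearance as the reference.** Background, primary aim: "ICG clearance will be used as a reference measurement of post-operative liver function and correlated against DGE-MRI before surgery". The next sentence of that section uses the same term for the pre-operative comparison with WL-GC. The Power calculation section sets ICG-C equal to 10 times FLR-GC plus error. ICG-C is not in the abbreviation list; I read it as ICG clearance.

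**The outcome measures name R15.** Primary objective: "The primary outcome measure is the correlation between preoperative FLR-GC (mL/min/kg) and ICG R15 1 day after surgery". Secondary objectives: "The outcome measure is the correlation between preoperative WL-GC (mL/min/kg) and a simultaneously measured ICG R15". The Abstract and the Data analysis section also use R15, which the abbreviation list explains as retention at 15 minutes.

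**Absolute concentration is obtained before surgery only.** The ICG measurement section says: "In order to derive absolute ICG concentrations, we will also take two separate blood samples of 2.5 mL each, both after ICG injection (pre-operative". The Blood samples section agrees ("Blood samples taken after ICG injection at the baseline visit will be processed in the LICAMM laboratories") and schedules a batch assay once recruitment is complete. In the PVE/ALPPS arm the second research visit repeats the baseline procedures, again before the resection. After resection, the In-patient follow-up section provides only for the bedside finger clip: "The ICG test with the finger-clip device will be repeated postoperatively at bedside to determine a reference value for postoperative liver function".

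No objective, outcome measure or analysis described in the article uses the absolute concentrations.

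**The concern.** The first secondary objective is meant to show that WL-GC measures what a recognised liver function test measures. If WL-GC is a clearance per kg and the comparator is a retained fraction, two patients with the same ICG clearance per kg will differ in R15 whenever their ICG volumes per kg differ. In the analysis that scatter looks like MRI error. R15 in percent also gives no slope in common units, so the validation cannot say whether the two clearances are proportional, or test the factor of 10 that the power calculation assumes.

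This is separate from the curved shape of R15. A rank correlation, or a transformation back to the rate constant, removes the curvature but leaves the volume in.

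**Working it through.** **The plan's own figure.** The 95% interval for the slope of ICG-C on FLR-GC is 9.12 to 10.88. Half-width: (10.88 − 9.12)/2 = 0.88, which is 8.8% of 10, as stated. The interval cannot be re-derived from scratch, because the log-normal parameters and the exact error scaling are not given. It describes the slope for ICG-C and does not carry over to a correlation with R15.

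**What R15 contains.** Assume one-compartment decay with clearance CL and distribution volume V, both per kg. Then C(t) = C(0) × exp(−t × CL/V), so

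R15 = C(15)/C(0) = exp(−15 × CL/V).

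The concentration scale cancels. R15 therefore needs no absolute concentration, and for the same reason it cannot yield a clearance. The weight-based bolus ("ICG will be administered intravenously as a bolus dose of 0.5 mg/kg through the cannula") does not remove V: C(0) = 0.5/V still depends on volume per kg. With the curve calibrated in absolute units, clearance per kg = 0.5/AUC, which is in mL/min/kg when AUC is in mg·min/mL.

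**Effect on single patients.** Same clearance, with V at 0.8, 1.0 and 1.2 times average (rate constants assumed):
- 0.10/min: exp(−1.875), exp(−1.5), exp(−1.25) = 15.3%, 22.3%, 28.7%.
- 0.07/min: exp(−1.3125), exp(−1.05), exp(−0.875) = 26.9%, 35.0%, 41.7%.

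**Effect on the correlation, perfect marker.** Let CL and V be log-normal and independent, with log-variance ln(1 + CV²). The correlation of log CL with the log rate constant is √[s²(CL)/(s²(CL) + s²(V))]. The rank correlation is (6/π) × arcsin(r/2), and R15 has the same ranks as the rate constant, reversed. The document gives none of these CVs; all are assumptions.

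Example, clearance CV 30% and volume CV 20%: √[0.0862/(0.0862 + 0.0392)] = 0.829, which gives a rank correlation of 0.82. Simulation gives the same values:

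| Volume CV | Clearance CV 30% | Clearance CV 50% |
|---|---|---|
| 10% | 0.94 | 0.98 |
| 20% | 0.82 | 0.92 |
| 30% | 0.69 | 0.84 |

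Against clearance itself, all of these would be 1.00. If volume and clearance are correlated at −0.3 to +0.3 on the log scale, the 20% row becomes 0.87 to 0.76 (clearance CV 30%) and 0.94 to 0.90 (clearance CV 50%).

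**Imperfect marker.** If the error in GC is unrelated to V, the log-scale correlations multiply. With GC-clearance correlation 0.8 (rank 0.79), clearance CV 40% and volume CV 20%: 0.8 × √[0.1484/(0.1484 + 0.0392)] = 0.8 × 0.889 = 0.711, rank 0.70. At volume CVs of 10% and 30% the ranks are 0.76 and 0.62.

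**The case against.** Much of the case on the other side stands.

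- **The terms may be loose rather than contradictory.** The ICG measurement section calls the finger-clip device a clearance meter, so the Background may use ICG clearance simply as a name for the test. The outcome sections are consistent in naming R15. This softens the conflict, but the power calculation still models a proportional relation that a retained percentage does not follow.
- **The article is condensed.** A reader might infer that the samples will go unused. The article does not support that: it gives their purpose and schedules the assay, and the full protocol or analysis plan may use them. What the article does fix is R15 as the validation comparator.
- **Volume variation is assumed.** A reader might take the 250 kg weight limit as evidence of wide variation in volume per kg. It is not: it is listed among the MRI contraindications, beside a limit on body diameter, and says nothing about the weights of the cohort.
- **A per-kg comparison has its own bias.** Dividing both clearances by the same weight can create correlation. Illustration with assumed values: two absolute clearances unrelated to each other and to weight, log-SD 0.3 each, log-SD of weight 0.2. The per-kg correlation is 0.04/(0.09 + 0.04) = 0.31 from weight alone, and less if clearance scales with weight. R15 has no weight denominator. This stands and shapes the fix.
- **Converting the day-1 rate constant with the pre-operative volume is tempting.** It would assume that ICG volume is unchanged across a liver resection, which nothing in the document supports. Sample times are not given either, so whether the two samples allow back-extrapolation is unknown.
- **No success threshold is stated.** No decision in the article visibly turns on the loss, and R15 remains a legitimate measure of liver function.

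**Conclusion.** The point holds as a low-cost improvement to the validation and a wording mismatch to reconcile. The aims and the power calculation speak of ICG clearance; the outcomes use R15; and the pre-operative concentrations that could bridge the two are tied to no stated outcome. Under one-compartment decay, and provided the error in GC does not itself follow ICG volume, variation in volume can only lower the correlation of WL-GC with R15.

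The size is unknown. For a perfect marker the loss is about 2-6% if the volume CV is 10%, and 8-18% if it is 20%. A reader might infer that the trial will understate agreement by a material amount; the document gives no volume variation, so that is not shown. Nor does the point make the primary outcome invalid. It limits what a correlation with post-operative R15 can say about clearance.

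**What to change.** 1. **Secondary objectives, validation outcome.** Alongside R15, pre-specify the correlation and slope of WL-GC on pre-operative ICG clearance, calculated from the administered dose and the finger-clip curve calibrated with the two blood samples. Report it both per kg and unnormalised (mL/min), because the shared body-weight denominator can inflate the per-kg correlation.
2. **Background aims and Primary objective.** State that the post-operative reference is a finger-clip disappearance measure (R15 or its rate constant), not a clearance in mL/min/kg, and give this as a limitation of the primary comparison. Do not convert the day-1 value with the pre-operative volume.

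Cost: some rewording and a little more analysis. No new sample, visit or dose is needed. Because the assay runs in batch after recruitment ends, the analysis can be fixed before any absolute concentration is known. Participants without usable samples contribute to the R15 comparison only.

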##### MRI scanning

The MRI will be performed straight after ICG measurement in 3 T Siemens (Erlangen, Germany) Magnetom Prisma scanner by radiographers of the department. The scan will last max 1.5 h and will include the injection of a standard dose of MRI contrast agent Gadoxetate 0.1 ml/kg (Primovist, Bayer AG). The same cannula will be used to administer he MRI contrast as for the ICG test. Other scans that will be taken in the same session include precontrast T1- and T2-weighted anatomical imaging, T2*-mapping, T1-mapping, proton-density fat fraction and post-contrast T1-weighted anatomical imaging.

#### Routine clinic visit

After completion of their MRI some participants will require re-discussion in the MDT and all participants will attend for a preoperative clinic appointment (see Fig. 1). A proportion of participants will not progress to surgery due to clinician or participant choice; these participants will not be followed up further. But the data that has already been collected will be used for addressing the secondary objective.

#### Intraoperative measurements

Intraoperative measurements of the resected liver segments will be taken, including weight and volume (measured using fluid displacement). The weight measurement is a routine procedure, but the volume measurement will be done for research purposes only.

#### In-patient follow-up

Once the participant’s surgery is complete, data obtained as part of the participant’s standard intra and post-operative care will be collected. This includes any blood tests during admission, the characteristics of the operation, complications and length of stay. Pathology results will be collected once reported. The ICG test with the finger-clip device will be repeated postoperatively at bedside to determine a reference value for postoperative liver function. This will be performed on day 1 post-surgery if feasible. A range of biochemical measures will be used to calculate postoperative liver function using the post-operative data set.

#### 90-day follow-up

After discharge all participants who underwent surgery attend the hospital for a routine post-operative clinic appointment after 90 days. Data from this appointment will be collected by the clinical research fellow, including complications, re-admissions and mortality.

### Study procedures (PVE/ALPPS arm)

Participants requiring PVE/ALPPS will be recruited in the same way as participants in the resection arm. They will attend the same baseline visit and the routine clinic visit. Participants may decline the PVE/ALPPS at this point, or the clinician may decide it is inappropriate at the clinic appointment. If this occurs and the participant proceeds to surgery, they will remain in the study. If they do not proceed to surgery their data will be used to address the secondary objectives.

A participant who does proceed to PVE/ALPPS will attend the hospital for a routine CT scan after the first stage, and a second research visit will be scheduled at that point. This visit will proceed in the same manner as the baseline visit. They will be re-discussed in the MDT and come for a preoperative clinic appointment. Participants may be deemed ineligible for surgery, or make the decision not to proceed with surgery, in which case their data already collected can feed into the secondary objectives. If they do proceed to surgery, the same intra-operative and post-operative data will be taken as for the resection arm.

### Management of data and samples

#### Patient-identifiable data

All physical paperwork with identifiable data will be stored in a secure location in St James’s Hospital. Electronic records with identifiable data will be encrypted, password protected and stored on the hospital’s secure servers. This includes a single key file containing the link between patient ID and anonymous study ID. Identifiable MRI data will also be stored in the secure Picture Archiving and Communication System (PACS) of the radiology department. Identifiable data will not be accessed by researchers outside of the clinical care team and are only retained for quality control, backup, and to follow-up on any incidental findings.

#### Pseudo-anonymised study data

Data collected for research purposes will be recorded using the participant’s anonymous study ID, in a single file per patient (See Clinical Data points supplementary file 1). Data will subsequently be transferred to an excel sheet for statistical analysis. Paper forms will be stored in a secure location in St James University Hospital. Electronic data will be stored in a participant study record in a secure database on an NHS workstation, and in password protected network drives set up and maintained by University IT. MRI images will be transferred anonymously from the scanner to the university’s database, where they will be analyzed by a research fellow to extract the imaging biomarkers. The original MRI data will be retained the university’s database to enable future secondary analyses.

